## Abstract

Obsessive-compulsive disorder (OCD) is a debilitating disorder with an approximate lifetime prevalence of 1–3%. Despite advances in leading treatment modalities, including pharmacotherapy and psychotherapy, some cases remain treatment resistant. Non-invasive brain stimulation has been explored in this treatment-resistant population with some promising findings; however, a lack of methodological rigor has reduced the quality of the findings. The current paper presents the protocol for conducting research into the efficacy of transcranial direct current stimulation (tDCS) in the treatment of OCD. A double-blind randomised controlled trial (RCT) will be conducted involving active tDCS vs. sham tDCS on 40 general OCD patients. The intervention consists of 2 mA anodal stimulation over the pre-supplementary motor area (pre-SMA) with the cathode positioned over the orbitofrontal cortex (OFC). Participants will receive 10 sessions of 20 min of either sham- or active-tDCS over 4 weeks. Outcomes will be categorical and dimensional measures of OCD, as well as related secondary clinical measures (depression, anxiety, quality of life), and neurocognitive functions (inhibitory control, cognitive flexibility).

## 1. Introduction

The frontostriatal model suggests that the symptoms of obsessive-compulsive disorder (OCD) are associated with dysfunction in the feedback loop, which leads to hyperactivity in the orbitofrontal cortical (OFC) pathways. As a result, individuals pay more attention to threatening stimuli. Neurological studies indicate that OCD symptoms are associated with increased neuronal activity in the OFC [1,2,3] and decreased activation in the pre-supplementary motor area (pre-SMA) [4] responsible for inhibitory control. Changes in patterns of activation (both hyperactivity and hypoactivity) in the frontal and motor cortices have been reported in a range of neuropsychiatric disorders, including ADHD and schizophrenia [5]. It has been suggested that an imbalance in cortical activation may underlie OCD [6,7,8]. With this in mind, several studies have attempted to address this imbalance in neuronal activation using non-invasive brain stimulation.

Transcranial direct current stimulation (tDCS) is a non-invasive stimulation technique used to modulate cortical activity and, as a consequence, change behaviour [9]. tDCS delivers low intensity electrical currents to modulate neuronal activity [10]. tDCS works by applying a positive (anodal) or negative (cathodal) current via electrodes to a targeted brain area. The current modifies cortical excitability by facilitating the depolarisation or hyperpolarisation of neurons respectively. Research in healthy individuals has found that anodal (excitatory) tDCS over frontal areas improves cognitive functioning [11,12]. Lawrence [13] reported that anodal tDCS over frontal areas led to improved cognition in those with Parkinson’s disease.

Although there is limited research in brain stimulation interventions for OCD, preliminary studies involving tDCS for patients defined as resistant to both CBT and pharmacotherapy have been encouraging. Hazari [7] conducted an open-label study using anodal tDCS over pre-SMA to increase pre-SMA activation, and with the cathode over OFC to decrease OFC activation. The patient, who was on escitalopram and clonazepam, received 2 mA of current for 20 min, twice a day for 10 days (20 sessions). This tDCS montage was based on the theory that OCD is due to deficient pre-SMA response inhibition on frontostriatal function [4,14]. The patient demonstrated an 80% reduction in OCD symptom severity, which was maintained for 7 months post-intervention with minor fluctuations. Whilst the patient did relapse at the 7-month time point, their symptoms improved following a further 8 sessions of tDCS. On both occasions that tDCS was applied, the patient’s OCD symptoms had remitted within 5–10 days. Narayanaswamy [8] used the same tDCS protocol combined with therapeutic SSRIs in two patients, who received 2 mA of current for 20 min, twice a day for 5 days (10 sessions). Both patients demonstrated significantly reduced OCD symptom severity (52% and 46.7% reduction) that was maintained at 1 and 2-month follow-up assessments. However, despite a few studies reporting positive effects of tDCS on OCD, the efficacy of non-invasive brain stimulation remains ambiguous [6], and there is a lack of consensus regarding stimulation protocols in regard to frequency, dose, intensity, and electrode montage/positioning. Further, there are several limitations associated with the published studies. 

Many of the tDCS and OCD studies published are single-patient case studies, and only two have included more than 10 participants [15,16]; thus, the results are not generalisable. No study to date has included a sham-control group. Few studies used an OCD symptom measure as the primary outcome, and those that did not indicate whether a change in the OCD symptom measure was clinically significant. Other aspects of functioning such as quality of life, inhibitory control, and cognitive flexibility have not been explored. Brunelin [6] conducted a systematic review of studies examining tDCS for those with OCD and concluded that although a number of studies demonstrated improvements in OCD, there was a lack of methodological rigor that reduced the quality of the findings.

## 2. Materials and Methods

The proposed clinical trial (ACTRN12620000990921) will be a double-blind randomised sham-controlled trial of tDCS for OCD to examine the therapeutic potential of tDCS for OCD symptoms. To the best of our knowledge, there has not been a double-blind sham-control randomised controlled trial (RCT) of tDCS for OCD, limiting conclusions about the effectiveness of this treatment approach.

### 2.1. Hypotheses

We hypothesise that active tDCS over the pre-SMA and OFC will be associated with a clinically and statistically significant decrease in OCD symptoms and beliefs, a significant decrease in comorbid depression and anxiety symptoms (if present), and a significant increase in quality of life. We also propose there will be improved inhibitory control and cognitive flexibility.

### 2.2. Participants

#### 2.2.1. Sampling

Recruitment of participants will occur through several channels. Primary recruitment will occur via the Curtin University Psychology Clinic, which houses a specialist OCD service, whereby promotional material will be distributed to suitable clients. A media release will be made through Curtin University, and private clinics specialising in OCD will be contacted/informed about the project and sent copies of advertising materials. Individuals who wish to take part in the study will follow instructions on the promotional material to contact the researcher. Interested participants will then be sent an information pack and consent form. Potential participants will be telephone-screened for tDCS suitability and will undergo a risk assessment in relation to the exclusion criteria prior to commencing the study. Participants who meet the inclusion criteria will then be contacted by the researcher to confirm their willingness to participate, inform them of start dates, offer them the opportunity to ask questions, and arrange the pre-treatment (baseline) assessment of outcomes. Following the post-intervention assessments (after session 10), a time will be scheduled for the 3-month and 6-month follow-up outcome assessments.

#### 2.2.2. Inclusion Criteria

Participants aged over 18-years with obsessive and/or compulsive behaviours who meet the criteria for the clinical diagnosis of OCD 300.3 (F42.2) in accordance with the Diagnostic and Statistical Manual of Mental Disorders (DSM-5; [17], using the Mini-International Neuropsychiatric Interview—Version 7.0.0 (MINI) [18].A minimum Yale-Brown Obsessive-Compulsive Scale (Y-BOCS) total score of 16, representing a minimum of moderate symptom severity.Participants taking medications (SRI/SSRIs) to manage OCD symptoms will be included as long as the dose has been stable for at least 12 weeks prior to participation [19] and they do not plan to change the dose during the study.

#### 2.2.3. Exclusion Criteria

Participants with a recent history of brain surgery, neurological conditions associated with brain abnormalities (e.g., traumatic brain injury; recent stroke, tumour), implanted cranial devices, hearing aids (unless they can be removed), or active skin lesions on the scalp.History of migraine, epilepsy, seizures, unstable medical and/or psychiatric conditions; history of psychosis or bipolar disorder; high suicide/self-harm risk.Current or past (within the last 1 month) use of benzodiazepines, anticonvulsants, lithium carbonate, psychostimulants, dextromethorphan and pseudoephedrine; recreational drug use.Currently undergoing Exposure and Response Prevention (ERP) therapy for OCD; any neuromodulation therapy (e.g., ECT, transcranial magnetic stimulation, tDCS) within the last 3 months.

#### 2.2.4. Randomisation

Participants will be randomly allocated to one of two treatment groups through block randomisation [20]: (1) active tDCS, or (2) sham tDCS. A computer-generated randomisation list will be used to allocate participants to groups at a ratio of 1:1 in blocks of four.

#### 2.2.5. Blinding

The investigators (researcher and supervisors) and the participants will be blinded to the group allocation. Each of the 40 participants will be allocated a personal identification (ID) number and be randomly assigned to either the active or the sham condition. The administrator (a third party) will create 40 protocols, each with the participant’s ID number, and load them onto the device. The procedure will be password-protected, and the researcher (operator) will not have access to the password. Once the double-blind mode is activated on the device, all non-essential information is hidden on the monitor, keeping the operator unaware of which protocol refers to active stimulation and which protocol is sham. When a participant arrives for their session, the operator will select the protocol number that corresponds to the participant’s ID number on the tDCS device and will not know which condition they have been allocated to.

## 3. Study Design

Stimulation will take place in the Curtin Psychology Clinic, where tDCS will be administered by the researcher. All participants will complete ten 20-min sessions of either active or sham tDCS stimulation over 4 weeks (all outcome-measures to be conducted pre- and post-intervention, and at 3- and 6-month follow-ups) (Table 1).

Participants will be seated in a comfortable armchair whilst receiving tDCS, which will be delivered for 20 min using a battery-driven (Necbox) multi-channel direct current stimulator, namely Starstim 20^TM^ (Neuroelectrics, Barcelona, Spain). Stimulation will be administered over the scalp via two 25 cm^2^ Sponstim electrodes (Neuroelectrics, Barcelona, Spain). The electrodes consist of a sponge cover, a carbon rubber core, and a nickel-plated brass metallic pin. The external surface of the sponges will be soaked in 5 mL of 0.9% saline solution to minimise the risk of skin irritation, and inserted into Fz (pre-SMA) and Fp1 (OFC) of an adult-sized neoprene cap (S, M, or L), which is pre-labelled according to the 10–20 EEG system of electrode positioning. The participant’s head will be measured to locate Cz (mid-line central part of the head), and then the cap will be placed on the participant’s head. Once the cap is in the correct position (with Cz lined up), it will be secured in place with a chin strap, and the medical sockets will be connected to the electrodes. An impedance check will be conducted to ensure optimal conductivity. If the impedance level is high, more saline solution will be added onto the surface of the sponges by inserting a curved syringe through a hole in the cap near the electrode.

Each session will involve 20 min of either active or sham stimulation. The tDCS montage (stimulation site, intensity, duration, and frequency) is informed by Kekic’s 2016 systematic review [21]. The participants in the active group will receive a constant current 2 mA stimulation via the anode placed over the pre-SMA and cathode placed over the left OFC. The anode will increase neural activation of the pre-SMA and the cathode will decrease neural activation of the left OFC (Figure 1). For the sham stimulation, the electrode montage will be identical to the active tDCS group; however, the participants will only receive tDCS for 30 s at the start, ramp up (0–2 mA) and end, ramp down (2–0 mA) of the session. This allows the participants to experience some sensation of tDCS. All participants (active and sham) will be informed that they may or may not perceive any sensation during the treatment, a procedure that has been demonstrated to effectively blind participants and the researcher to the stimulation condition they are in [22].

### 3.1. Outcome Measures

Diagnostic screening, neuropsychological, and cognitive assessment measures for this study will be administered at baseline, post-intervention, 3-month-, and 6-month follow-up. The Y-BOCS, Depression Anxiety Stress Scales (DASS-21), and Obsessive Beliefs Questionnaire (OBQ-44) will also be administered at the end of the 1st, 2nd, and 3rd week of the intervention period to identify if, and when, changes may occur. OCD symptom change, as measured by the Y-BOCS, is the primary outcome being assessed in this study.

Diagnostic screening: The MINI-7.0.0 [20] will be used for clinical diagnosis of OCD.

OCD symptom severity: The Y-BOCS [23] measures symptom type and severity over the last 7-day period and consists of two 10-item subscales, namely obsessions and compulsions. 

Negative affect: The Depression Anxiety Stress Scales (DASS-21) [24] is a self-report measure to identify and measure negative affect (if present).

Quality of life: The Quality of Life Enjoyment and Satisfaction Questionnaire-Short Form (Q-LES-Q-SF) [25], also a self-report measure, has 16 items evaluating overall enjoyment and satisfaction with physical health, mood, work, household and leisure activities, social and family relationships, daily functioning, sexual life, economic status, overall well-being, and medications.

OCD beliefs: The Obsessive Beliefs Questionnaire (OBQ-44) measures OCD beliefs. The OBQ-44 includes (1) perfectionism and intolerance of uncertainty, (2) importance and control of thoughts, (3) responsibility, and (4) overestimation of threat, which are positively associated with obsessive-compulsive symptoms and worry [26].

Inhibitory function: The Stop Signal Task is a choice go/no-go reaction-time task to measure inhibitory control. In this computerised task, participants are required to discriminate between left and right arrows by pressing the appropriate response key as fast as possible (go), but inhibit their motor response if a beep is played after the presentation of the arrow (no-go) [27]. The task is designed so that the frequency of the ‘go’ cues are greater than the ‘no-go’ cues, resulting in the ‘go’ response becoming prepotent and thus control being required to inhibit/withhold the response [28].

Cognitive flexibility: The set-shifting task will be used to measure cognitive flexibility. Set-shifting measures the ability to shift attention and respond to a particular aspect of a stimulus depending on a reinforced contingency. The rules or contingencies of the task change and alternate rapidly, requiring the participant to pay attention and respond with the pertinent rule in mind, switching from the old to the new rule. Individuals with OCD demonstrate repetitive and perseverate behaviour, and impairments in set-shifting ability have been reported to be a key neurocognitive feature of OCD [28,29].

### 3.2. Potential Side Effects

The procedure is considered very low risk, and no significant adverse events have been reported with low-current procedures such as the ones proposed in this study. Potential side effects of low-current tDCS include localised scalp itching or tingling sensation at the site where the electrode was placed, and seldom-occurring headache or fatigue [30]. If any of these side effects occur, the participant will be monitored; if they do not dissipate within 1 hour (the typical duration of symptoms/s), the participant will be referred for assessment by a medical practitioner. Any adverse side effects will be reported to the appropriate ethics committee. Discontinuation and/or withdrawal from the study will be recorded in the study database.

### 3.3. Data: Sample Size, Management, Analysis

This study will provide evidence for the efficacy of the treatment approach, which may in turn lead to effectiveness trials for clients with more complex or particular OCD profiles. There are no suitable tDCS trials to guide a power analysis for this study; however, a G*Power calculation indicated that 30 participants (15 per group) are required to detect a moderate effect (α = 0.05; power = 0.80). We will aim to recruit 40 participants (20 per group) to allow for attrition.

A series of generalised linear mixed models (GLMMs), one for each of the seven outcome measures, will be used to determine whether active and sham tDCS differ at pre- versus post-intervention in the outcome measures. The GLMMs will be conducted using the GENLINMIXED procedure in SPSS (Version 26). GLMMs are used to control for outcome variables when the data are not normally distributed and include random and fixed effects [31]. This study has one nominal random effect (participant) and one nominal fixed effect (group: tDCS vs. sham), one ordinal fixed effect (time: pre-intervention, post-intervention, and 3- and 6-month follow-up), and the group x time interaction. GLMMs are robust against unequal groups [32], and unlike ANOVAs, GLMMs do not rely on participants providing data at each assessment point, reducing the effect of participant attrition on statistical power.

This study will conform to the guidelines under Section 2 of the Australian Code for Responsible Conduct of Research. All hard data (diagnostic screening, consent forms, psychometric measures) will be stored in a clinic file as part of the current clinic procedures. Data will be extracted and stored in a de-identified manner separate from the clinic file. Deidentified data will be shared if required by a journal. All electronic data will be password-protected, stored on the Curtin research drive, and backed up on an external hard drive, which will be kept in a locked drawer. Data will be kept for a minimum of 25 years, as per the Western Australian University Sector Disposal Authority (WAUSDA) guidelines for clinical trials, and only the researcher and supervisors will have access to data.

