## Figures and Tables

**Figure 1 brainsci-10-01008-f001:**
[figure not shown]
A 3D standardised model of the estimated electric field generated from anodal stimulation over Fz with the cathode placed over Fp1. This model was produced using the Neuroelectric Stim 20^TM^ Preview function.

**Table 1 brainsci-10-01008-t001:** Transcranial direct current stimulation (tDCS) protocol and assessment of outcome measures.

Outcome Measures	Week 1			Week 2			Week 3			Week 4			Follow-Up	
	Pre-Intervention Assessment	10 Sessions of tDCS (Active or Sham)										Post-Intervention Assessment	3-mth	6-mth
		S1	S2	S3	S4	S5	S6	S7	S8	S9	S10			
	T1		T2			T3			T4			T5	T6	T7
MINI	x											x	x	x
Y-BOCS	x		x			x			x			x	x	x
DASS 21	x		x			x			x			x	x	x
OBQ-44	x		x			x			x			x	x	x
Q-LES-Q-SF	x											x	x	x
Stop-Sig	x											x	x	x
Set-Shifting	x											x	x	x

Note. tDCS stimulation protocol for the active and sham groups involves 10 sessions conducted over 4 weeks. Participants attend the clinic three times per week with all outcome measures (x) assessed at 4 timepoints (T). Pre-intervention/baseline on day 1, post-intervention 2 days after the final tDCS session (S) S10, and follow-up measures at 3 and 6 months (mth). The Yale-Brown Obsessive Compulsive Scale (Y-BOCS), Depression Anxiety Stress Scales (DASS-21), and Obsessive Beliefs Questionnaire (OBQ-44) will also be administered at the end of week 1 (T2), week 2 (T3), and week 3 (T4) of the intervention period to monitor changes in symptom severity and/or sub-domains.

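### If the MINI is one of the seven outcomes, the planned pre-versus-post group comparison has no finite estimate for OCD diagnosis, because every participant is positive at baseline by entry criterion

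*Protocol article*

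**What the plan says.** Section 3.3 plans "A series of generalised linear mixed models (GLMMs), one for each of the seven outcome measures". The models "will be used to determine whether active and sham tDCS differ at pre- versus post-intervention in the outcome measures". Their terms are a participant random effect, group, "one ordinal fixed effect (time: pre-intervention, post-intervention, and 3- and 6-month follow-up), and the group x time interaction". No outcome is exempted, and the seven are not named.

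The only list headed as outcome measures is Table 1. Its rows are MINI, Y-BOCS, DASS 21, OBQ-44, Q-LES-Q-SF, Stop-Sig and Set-Shifting: seven with the MINI, six without it. The MINI is marked at T1, T5, T6 and T7, which are the four time levels of the section 3.3 model. Section 3 also speaks of "all outcome-measures to be conducted pre- and post-intervention, and at 3- and 6-month follow-ups", and the abstract announces that "Outcomes will be categorical and dimensional measures of OCD".

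Section 2.2.2 admits only people "who meet the criteria for the clinical diagnosis of OCD 300.3 (F42.2") as established with the MINI.

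**The concern.** The instrument that decides entry is also, on the best reading, an outcome analysed for change from entry. At T1 it cannot vary: every participant in both arms is positive. A model for a yes/no outcome with T1 as a time level must then estimate a log-odds for a proportion of exactly 1, which is infinite. The comparison that section 3.3 names is a contrast against that level.

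At stake is how the result on OCD diagnosis is read. The software may fail to converge, or may print an interaction with a very large standard error and a p-value near 1. The second outcome could be reported as no effect on diagnosis, even if the arms differ clearly after treatment.

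**Working it through.** **Inputs.** From the document: seven outcome measures (section 3.3); seven rows in Table 1 including the MINI; 20 per arm (section 3.3); all positive at T1 (section 2.2.2). Assumed: a binary outcome with a logit link, since section 3.3 states no distribution or link; and 8/20 active and 18/20 sham still diagnosed at T5. The document gives no post-intervention rates.

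**Step 1: the count.** Table 1 gives 1 (MINI) + 6 others = 7, which matches section 3.3. Without the MINI it gives 6.

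**Step 2: the T1-to-T5 interaction.** For a logit model with one parameter per group-by-time cell, the interaction is

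[logit p(active, T5) − logit p(active, T1)] − [logit p(sham, T5) − logit p(sham, T1)],

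and its variance is the sum over the four cells of 1/[n p(1 − p)].

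- The two T5 cells contribute 1/8 + 1/12 + 1/18 + 1/2 = 0.764.
- Each T1 cell contributes 1/[20 p(1 − p)], which grows without limit as the fitted p approaches 1.

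Fitting from zero by iteratively reweighted least squares, with the information evaluated at the updated estimate:

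| Iterations | Fitted p at T1 | SE of interaction | Wald p |
|---|---|---|---|
| 5 | 0.99797 | 7.09 | 0.71 |
| 12 | 0.999998 | 232.8 | 0.99 |
| 20 | 1 − 6 × 10⁻¹⁰ | 12,710 | 1.00 |

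Check at 5 iterations: 1/(20 × 0.99797 × 0.00203) = 24.7 per T1 cell; 2 × 24.7 + 0.764 = 50.2; square root 7.09. The printed coefficient of −2.60 arises only because both T1 logits climb in step; the limit is infinity minus infinity. The exact SE at a given iteration depends on starting values and counting. The divergence does not.

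**Step 3: a likelihood-ratio test does not help.** With T1 and T5 only, a model without the interaction already fits perfectly in the limit: the T1 logit goes to infinity, and the group term reproduces the T5 difference. The likelihood-ratio statistic for the interaction is therefore 0. With all four levels, the interaction test reflects only whether the arm difference changes among T5, T6 and T7. A constant benefit at those visits goes into the group term.

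**Step 4: what remains estimable.** The active-minus-sham contrast at T5 is ln(8/12) − ln(18/2) = −0.405 − 2.197 = −2.60, with SE √0.764 = 0.87, z = −2.98 and p = 0.003. In a fixed-effect fit with all four levels (assuming also 9/20 and 10/20 active, 17/20 and 17/20 sham at T6 and T7) this contrast is the same at 5, 12 and 20 iterations. The change in arm difference between T5 and T7 is also stable (−0.87, SE 1.16). Fisher's exact test at T5 gives p = 0.0022.

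**Step 5: dependence on the assumed counts.** Over all 361 T5 tables with 1 to 19 positives per arm (19 × 19), the Wald test of the T1-to-T5 interaction after 15 iterations is significant at 0.05 in none. Fisher's test at T5 is significant in 152. Under assumed true rates of a positive diagnosis (sham versus active, 20 per arm), Fisher's power is 0.72 for 0.95 v 0.60, 0.74 for 0.90 v 0.50, 0.91 for 0.90 v 0.40 and 0.997 for 0.95 v 0.30. The interaction test has power 0 in the last three, where it was computed.

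**Step 6: the random intercept.** In one simulated data set with a participant random intercept, the log-likelihood keeps rising as the T1 logit is moved from 4 to 12 (−43.79 to −39.80). The T1-to-T5 interaction z shrinks from −2.30 to −0.63, while z for the T5 arm contrast only moves from −3.13 to −2.61. The random effect does not cure the problem.

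**The case against.** **The MINI may not be one of the seven.** Section 3.3 does not list them. The hypotheses in section 2.1 can also be counted to seven without it: OCD symptoms, beliefs, depression, anxiety, quality of life, inhibitory control and cognitive flexibility. Section 3.1 describes the MINI only as a diagnostic instrument, and no hypothesis mentions loss of diagnosis. This stands as a caution, and MINI membership is an inference. It remains the better reading: depression and anxiety come from one instrument, the DASS-21, which is a single row in Table 1, and the note to Table 1 has participants attending "with all outcome measures (x) assessed at 4 timepoints (T"), which includes the MINI. Nor does the document say that diagnosis is the only categorical OCD outcome; a Y-BOCS response category is possible.

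**The model is not lost.** A reader might infer that no group-by-time term can be estimated, or that the model must miss a real effect. Step 4 shows otherwise: only the T1 cells and contrasts against them diverge, and the T5 arm contrast from the same fit finds the effect. What fails is the contrast that section 3.3 names as its question.

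**The link is for the analysis plan.** Section 3.3 gives no distribution, so the logit is an assumption. On the proportion scale the contrast is finite: (0.40 − 1) − (0.90 − 1) = −0.50. That is just the T5 difference, so baseline adds nothing there either. The absence of a link is not the complaint. The article itself fixes the time levels, the contrast and the count, without an exception for an outcome that cannot vary at T1.

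**Conclusion.** The point holds in limited form. If the MINI is among the seven and is analysed as a binary outcome, the pre-versus-post group contrast has no finite estimate and no power, whatever the post-intervention rates. Comparing the arms after baseline does have power for large differences: 0.72 to 0.997 in the four assumed scenarios with 20 per arm.

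It does not reach further. Section 3.1 makes Y-BOCS change the primary outcome, and that analysis, the other score and task outcomes and the sample size are untouched. A reader might take this as a threat to the trial's efficacy conclusion; the document does not support that. It is a flaw in the analysis of one secondary outcome, worth correcting because it could yield an uninterpretable null on diagnosis and costs almost nothing to remove.

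**What to change.** In section 3.3, name the outcome measures and take the MINI out of the common pre-versus-post model. For OCD diagnosis (present or absent), compare the arms at T5 by the difference in proportions with an exact or score 95% confidence interval and Fisher's exact test, and treat T6 and T7 likewise. A binary mixed model on T5 to T7 with no pre-intervention level is an alternative, but it meets the same difficulty if an arm is wholly positive at a later visit. With 20 sham participants and an assumed rate of 0.90 to 0.95, that chance at any one visit is 0.90²⁰ = 0.12 to 0.95²⁰ = 0.36. The proportions approach is therefore the safer main analysis.

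If the MINI is not meant to be one of the seven, correct the count, or say which measure is split to reach it, and state what the repeated MINI assessments are for.

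The cost is a few sentences. No extra data, visits or participants are needed.

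### Modelling baseline as a free level of time makes the pre-post comparison a difference in raw change, which is valid but usually less precise than adjusting for the baseline score

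*Protocol article*

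**What the plan says.** Section 3.3 sets out the model term by term. "This study has one nominal random effect (participant) and one nominal fixed effect (group: tDCS vs. sham") is followed by an ordinal fixed effect, given as "time: pre-intervention, post-intervention, and 3- and 6-month follow-up), and the group x time interaction". The models "will be used to determine whether active and sham tDCS differ at pre- versus post-intervention in the outcome measures".

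Pre-intervention is therefore one of four levels of the response. The group main effect gives each arm its own baseline mean. The article states neither a baseline covariate nor a constraint that the arms share a baseline mean.

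Table 1 shows every measure taken at T1, so the baseline score needed for adjustment will be in hand. On sample size, section 3.3 says that "a G*Power calculation indicated that 30 participants (15 per group) are required to detect a moderate effect (α = 0.05; power = 0.80"), and the target is raised to 40 to cover attrition.

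**The concern.** Allocation is randomised 1:1, so the two arms have the same expected baseline. Estimating a separate baseline mean for each arm and subtracting it carries the chance baseline difference into the treatment effect at full weight. Adjustment gives that difference only the weight that the baseline-to-outcome correlation supports.

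The trial plans 15 to 20 participants per arm, and the Discussion says its result will inform whether to go on to larger trials. Precision that can be had from data already scheduled is worth keeping. The article writes out the model, so adjustment would change a stated analysis and not merely fill in detail left to a later plan.

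**Working it through.** **Inputs from the article.** 15 per arm required and 20 per arm recruited (section 3.3); 1:1 allocation (section 2.2.4); α = 0.05 and an effect described only as moderate (section 3.3).

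**Assumptions.** The article gives no baseline-to-post correlation (rho), no SD, no numerical effect size and no sidedness. I take a two-sided test, d = 0.5 for a moderate effect, a continuous outcome with an identity link, and rho over a range.

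**The plan's own figure.** The total of 30 cannot be uniquely reproduced, because neither the test nor the effect size is given. A two-sample t test at d = 0.5 needs 64 per group. A repeated-measures group-by-time interaction at f = 0.25 needs 34, 28 or 24 in total for two, three or four times at rho 0.5, and 32 for four times at rho 0.3. The basis of 30 is a separate question, and nothing below depends on it.

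**Step 1: what the planned contrast is.** With complete data and a random participant intercept, the pre-post interaction coefficient equals the difference between arms in mean change. A fitted model on simulated data gave -0.0765 for both. The full interaction over four levels has 3 degrees of freedom and is a broader test. The identity applies to each contrast of a later visit with baseline, including the pre-post one that the article targets.

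**Step 2: variances per participant**, with SDs s1 (T1) and s2 (T5):
- planned: s1² + s2² − 2·rho·s1·s2
- adjusted: s2²(1 − rho²) × [1 + 1/(N − 4)], where the bracket is the small-sample price of estimating the slope. It is 1 + 1/26 = 1.038 at N = 30 and 1 + 1/36 = 1.028 at N = 40.

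**Step 3: equal SDs.** Without the bracket the ratio of adjusted to planned is (1 − rho²)/[2(1 − rho)] = (1 + rho)/2.

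| rho | large sample | N = 30 | N = 40 |
|---|---|---|---|
| 0.3 | 0.65 | 0.68 | 0.67 |
| 0.5 | 0.75 | 0.78 | 0.77 |
| 0.7 | 0.85 | 0.88 | 0.87 |

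Simulation (20,000 runs per setting) gave ratios of 0.67, 0.77 and 0.87 to 0.88, with both estimators unbiased. At rho 0.5, 40 participants analysed as planned carry about the information of 40 × 0.77 ≈ 31 analysed with adjustment.

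**Step 4: SD 5 at T1 and 7 at T5.** Planned variance is 74 − 70·rho; adjusted is 49(1 − rho²) times the bracket.

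| rho | planned | adjusted, no bracket | ratio, N = 30 | ratio, N = 40 |
|---|---|---|---|---|
| 0.3 | 53 | 44.59 | 0.87 | 0.86 |
| 0.4 | 46 | 41.16 | 0.93 | 0.92 |
| 0.5 | 39 | 36.75 | 0.98 | 0.97 |
| 0.6 | 32 | 31.36 | 1.02 | 1.01 |

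**Step 5: power at d = 0.5, equal SDs.** Noncentral t with noncentrality d/√(2v/n), where v is the variance in SD² units. At rho 0.5, v is 1.00 as planned; adjusted, it is 0.75 × 1.028 = 0.771 (n = 20) or 0.75 × 1.038 = 0.779 (n = 15).

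| rho | 20 per arm, planned → adjusted | 15 per arm, planned → adjusted |
|---|---|---|
| 0.3 | 26% → 36% | 20% → 27% |
| 0.5 | 34% → 42% | 26% → 32% |
| 0.7 | 51% → 57% | 40% → 44% |

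**The case against.** The strongest reply is that nothing is wrong with the plan. The contrast is valid under randomisation and it answers the question asked: section 3.1 names symptom change as the primary outcome, and section 3.3 asks about pre versus post. That is right as far as bias goes. It does not answer a point about precision, since with randomised arms the adjusted comparison estimates the same treatment effect.

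The second reply is that the size rests wholly on a correlation and SDs that the article does not give. This stands, and it is why a range is shown that includes no gain at all.

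Four stronger readings are tempting, and the documents support none of them:
- *The planned analysis is biased.* It is not; the simulated estimates centred on the true effect under both methods.
- *The trial misses its stated power, or adjustment brings it to 80%.* The article does not say how 30 was obtained, and some repeated-measures settings give totals near it. A larger effect such as d = 0.8 can be made to cross 80%, but the article names a moderate one.
- *Adjustment is free.* Baseline with its time interaction takes three coefficients over three later visits, and in the last row of Step 4 the variance rises by about 2%.
- *The Y-BOCS entry minimum of 16 enlarges the loss.* Under a linear model, selection on baseline leaves slope and residual variance alone and shrinks the baseline SD. Starting from SDs of 7 and 7 with rho 0.5 (ratio 0.75), cutting the baseline SD to 5 lowers rho to 0.38. The ratio becomes 36.75/(25 × 0.25 + 36.75) = 36.75/43 = 0.85, so the loss is smaller.

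The statement in section 3 that there will be "all outcome-measures to be conducted pre- and post-intervention, and at 3- and 6-month follow-ups" is only an assessment schedule. It does not bear on how baseline is modelled.

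**Conclusion.** The point holds as one of efficiency. As written, the model leaves the baseline means free and so compares raw change. Adjustment would reduce the variance of the pre-post treatment effect by an amount between nil and about one third (1 − 0.68 = 0.32), under the correlations and SDs assumed above. The gain is largest when the correlation is low and the SDs are equal, and it vanishes when the outcome SD clearly exceeds the baseline SD and the correlation is near 0.6. At rho 0.5 with equal SDs it is worth 6 to 8 percentage points of power for d = 0.5, which leaves power for that comparison well below 80% either way. The change is worth making because it costs little, but the planned result would remain valid without it.

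**What to change.** In section 3.3, for each continuous outcome, state one of two models:

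1. Keep T1 as a response and constrain both arms to a common T1 mean. This retains participants who have no score after baseline, in keeping with the article's reason for choosing mixed models.
2. Use the T1 score as a covariate with its interaction with time, and model only the post-intervention, 3-month and 6-month visits. This drops participants with no later score.

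In either case, report the adjusted active-minus-sham difference with its confidence interval at each visit. The two versions are close but not interchangeable. Besides the missing-data difference, the first takes its adjustment from the fitted covariance, so that covariance should let the variance differ between visits; a single participant intercept does not.

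The cost is one sentence, no new data, and up to three covariate coefficients, with a variance increase of about 2% in the least favourable scenario shown. The choice should be fixed before unblinding.
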